### Sample size calculation

Sample size calculation was based upon the reported differences in mean brachial artery FMD and cIMTs in children below 18 years of age in published literature [18] as well as our previous unpublished study in 52 children with NS and 50 healthy controls which looked at cIMT and FMD as the primary outcomes [19]. FMD and cIMT are the most validated indices of endothelial dysfunction and subclinical atherosclerosis in published literature [18]. Data on LDF for PORH in children remains limited. Reported values of mean (± SD) change from baseline of FMD in normal children between 9 and 16 years have ranged between 4.73 ± 4.38% to 7.7 ± 4.0% while the reported maximum mean cIMT in normal children below 18 years of age has been 0.50 + − 0.05 mm3.A.For Cross Sectional Comparisons during Phase I and II

Assuming a conservative estimate of minimum difference of FMD of 3% between normal and nephrotic syndrome with a standard deviation (SD) of 5%, a minimum of 46 cases each of NS and healthy controls will be required for a study with power of 80% at a two-sided 0.05 significance level. This sample size will be able to detect a difference of 0.03 mm of cIMT between children with NS and healthy controls with a power of 80% at a 0.05 significance level. With a 5% attrition rate due to mortality or loss to follow up for the entire study, a minimum sample size of 50 children with NS and 50 healthy children is proposed during phase I of the study. Any subsequent cases of incident/prevalent nephrotic syndrome presenting to the OPD after the 12 months recruitment phase gets over will also be added onto the repository for future analysis. Hence at end of 36 months of study, a minimum of 70 cases each of SSNS, SRNS and healthy controls will be required after final classification of phenotype of NS for a post-hoc Bonferroni adjustment for comparison of 3 means (2 groups of SSNS and SRNS compared to a control healthy group) of FMD and cIMT. Between the 2 participating institutions this number is expected to be available by 36 months of study.B.For Prospective Follow-Up during Phase II

For the phase 2 of study with prospective follow up for progression of endothelial dysfunction towards subclinical atherosclerosis as determined by cIMT as the gold standard, if total of 95 children (NS and controls) were to be followed for 24 months after an accrual period of 12 months, assuming a median time of 12 months for a detectable difference of cIMT of > 0.004 mm over 12 months between children with NS and healthy controls, the probability is 80% that the study will detect a difference at a two sided 5.0% significance level, if the true hazard ratio is 2.0. With these preceding assumptions again minimum of 50 children with NS and 50 healthy controls will need to be recruited and followed up over 24 months.

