### Phase ii: Prospective follow up and cardiovascular outcomes assessment

Children will be followed up to monitor the clinical course and undergo management of Nephrotic syndrome as per existing standard consensus guidelines [16, 17].Noninvasive assessment of biomarkers of endothelial dysfunction and subclinical cardiovascular comorbidities along with biochemical estimates of cardiovascular risk will be carried out at defined time points.At the end of 24 months from recruitment for a given case, final reclassification of disease phenotype based on the temporal profile of relapses/remission and steroid sensitivity will be done to categorize the subjects into the following categories as per standard definitions of Indian Society of Pediatric Nephrology [16, 17]: a. Steroid sensitive nephrotic syndrome (SSNS) b. Steroid resistant nephrotic syndrome (SRNS) c. Healthy controlsVenous blood plasma (in tubes containing EDTA (1.8 mg/ml) and citrated vials after centrifugation at 1500 rpm for 30 min at 4 degree Centigrade) and urine samples will be collected at baseline, 12 and 24 months and stored at − 80 C for batch assay of biochemical markers of endothelial dysfunction at a later date.

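### The 70 SSNS and 70 SRNS children expected with a final phenotype at month 36 can come only from children enrolled by month 12, when the plan commits to at least 50 with NS

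*Protocol article*

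**What the plan says.** All places are in the protocol article.

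- **Phase ii: Prospective follow up and cardiovascular outcomes assessment.** The final phenotype runs on each child's own clock: "At the end of 24 months from recruitment for a given case, final reclassification of disease phenotype based on the temporal profile of relapses/remission". Response to steroids also enters the grouping. The resulting categories are SSNS, SRNS and healthy controls.
- **Sample size calculation, part A, first recruitment figure.** "a minimum sample size of 50 children with NS and 50 healthy children is proposed during phase I of the study".
- **Same part, later cases.** Children with NS "presenting to the OPD after the 12 months recruitment phase gets over will also be added onto the repository for future analysis".
- **Same part, the target.** The next sentence draws its conclusion from this and dates it to the close of month 36. It says that "a minimum of 70 cases each of SSNS, SRNS and healthy controls will be required after final classification of phenotype of NS". The purpose is a Bonferroni-adjusted comparison of FMD and cIMT in SSNS and SRNS against controls. The two institutions are expected to supply the number by month 36.
- **Sample size calculation, part B.** Children are to be "followed for 24 months after an accrual period of 12 months", again with a minimum of 50 NS and 50 controls.
- **Abstract, Methods.** 70 SRNS, 70 SSNS and 70 controls are being recruited. No accrual window is given.

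**The concern.** The target carries a size (70 SSNS and 70 SRNS), a status (finally classified) and a date (month 36). The status takes 24 months per child to acquire. The route the plan describes from 50 NS children to 140 runs through children who enter after month 12, and they cannot acquire the status by that date.

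What is at stake is the three-group comparison, which is the reason given for raising the size to 70 per group. At month 36 it would either run on far fewer finally classified children than planned, or mix final phenotypes for early entrants with provisional ones for later entrants. The plan provides for neither.

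**Working it through.** **1. The plan's own starting figure.** Inputs from part A of the sample size section: FMD difference 3%, SD 5%, two-sided alpha 0.05, power 80%. The standardised difference is d = 3/5 = 0.6. The normal approximation gives 44 per group and the t-test 45, against the stated 46. Inflating for 5% attrition, 46/0.95 = 48.4, so 49, against the stated 50. Both are reproduced within 2 children.

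**2. The 70 per group.** The number of Bonferroni comparisons is not stated. At 80% power the normal approximation gives 53 per group for 2 comparisons, 59 for 3, 62 for 4 and 68 for 6. For 2 comparisons at 90% power it gives 69. So 70 is reachable under plausible choices, and the figure itself is not the problem.

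**3. The dates.** Month of final classification = month of enrolment + 24.

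| Enrolled at month | Finally classified at month | In the set at month 36? |
|---|---|---|
| 0 | 24 | yes |
| 12 | 36 | yes |
| 13 | 37 | no |
| 18 | 42 | no |
| 24 | 48 | no |

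The latest qualifying enrolment is month 36 - 24 = 12.

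**4. The numbers.**

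- NS children needed: 70 + 70 = 140. Stated minimum by month 12: 50. Gap: 90.
- Ratio: 140/50 = 2.8. Monthly rate: 140/12 = 11.7 against 50/12 = 4.2.
- With 5% attrition: 140/0.95 = 147.4, so 148 would have to enter by month 12, while a cohort of 50 would leave 50 x 0.95 = 47.5 to classify.
- Illustration, assuming accrual stays at 50 per 12 months: the 140th NS child enters at 140/4.167 = month 33.6 and is finally classified at month 57.6.
- Controls: 70 - 50 = 20 beyond the Phase I minimum. They have no steroid-response phenotype to await, but the sentence on later additions covers NS cases only, so part A names no source for these 20.

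**5. Power per contrast against controls.** Two-sample t-test, d = 0.6, noncentrality = 0.6 / sqrt(1/n1 + 1/n2). Alpha is 0.05/2 = 0.025 or 0.05/3 = 0.0167. The documents give no SSNS:SRNS ratio and no accrual forecast, so every row after the first is an assumption.

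| Phenotype group v controls | Noncentrality | alpha 0.025 | alpha 0.0167 |
|---|---|---|---|
| 70 v 70 (as planned) | 3.55 | 90% | 87% |
| 50 v 50 (100 NS classified, even split) | 3.00 | 76% | 71% |
| 25 v 50 (50 NS classified, even split) | 2.45 | 57% | 50% |
| 40 v 50 (50 NS classified, larger phenotype) | 2.83 | 71% | 65% |
| 10 v 50 (50 NS classified, smaller phenotype) | 1.73 | 29% | 24% |

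An uneven split helps one contrast and hurts the other. With 50 NS classified, neither contrast reaches 80% in any split shown.

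**The case against.** **50 is a floor, not a forecast.** The abstract says 70/70/70 are being recruited, and no accrual rate is given. If 140 NS children enter by month 12, the target is met. This stands, so it would be wrong to call the target impossible. It does not remove the conflict: part A moves from the later-presenting cases to the 70 per group with a word of consequence, and part B repeats 50 + 50 with 12 months' accrual. If the later cases are instead only for future analysis, the 90 extra NS children have no stated source.

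**The primary objective does not need the split.** It compares NS with healthy controls, and its FMD comparison is sized at 46, raised to 50, per group. The longitudinal sizing also uses 50 + 50 over 12 + 24 months and fits the dates. This stands in full and limits the point to the three-group comparison.

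Three stronger readings are tempting, and the documents do not support them.

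- *Baseline FMD will be compared between groups defined by the following 24 months.* No section says so. Part A covers cross-sectional comparisons in both phases without naming the visit. Month-24 measurements compared by month-24 phenotype would use no future information.
- *Children lost before month 24 have no group.* The Phase II section speaks of reclassification and the abstract describes children recruited as SRNS or SSNS, so an entry phenotype appears to exist.
- *Controls also miss the date because they await classification.* They are listed as a category at month 24, but they are deemed healthy at entry. Their gap is one of source, not of timing.

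**Conclusion.** The concern holds in a limited form. As written, the plan's route does not deliver 70 SSNS and 70 SRNS children with a final phenotype by month 36. The date arithmetic is exact and rests only on the plan's own statements. The shortfall is conditional: it is 90 of 140 NS children if recruitment in the first 12 months stops at the stated minimum, and it disappears only if all 140 enter in that window.

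The loss of power depends on assumed numbers and splits. At the stated minimum it runs from about 90% or 87% per contrast down to 57% or 50% with an even split, and to 29% or 24% for a phenotype with 10 children. At 100 NS children split evenly against 50 controls it is 76% or 71%.

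**What to change.** Reconcile the Phase II section with parts A and B of the sample size section.

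1. State that the finally classified set at month 36 consists of the children recruited in months 0 to 12, and give the power of the three-group comparison for the number expected.
2. Base the 70/70/70 comparison on the SSNS or SRNS status documented at recruitment, for all enrolled children. Keep the month-24 phenotype as a secondary analysis in children who have reached month 24.
3. Say where the 20 controls beyond 50 come from and by when.

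Alternatives that also reconcile the dates are to plan for all 140 NS children and 70 controls within the first 12 months, or to extend the study beyond month 36. Both are operationally heavier.

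The cost of the preferred change is wording and one recorded variable, the phenotype at entry. Its drawbacks are a less favourable stated figure for the final-phenotype comparison, and that some children will later change class, so the main and secondary analyses will not group every child alike.

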**Methods:**

In a multi-centric prospective cohort study, 70 Steroid Resistant NS (SRNS), 70 Steroid Sensitive (SSNS) patients along with 70 Healthy Controls are being recruited. After a baseline assessment of functional and structural status of heart (2D Echocardiography), arteries (Carotid Doppler and Intima Media Thickness measurements) and microcirculation [a combination of 2D Echocardiography, Laser Doppler Flowmetry (LDF) and Brachial Artery Flow mediated dilation (FMD) and Nail Fold Capillaroscopy (NFC)], the patients are being investigated for endothelial dysfunction. Venous blood sample (15 ml) is being collected for routine investigations and assay of biochemical endothelial markers through Flow Cytometry. The patients will be followed up at 12 months and 24 months after the recruitment to look for any change from baseline period.

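### The plan requires 70 children per group after the 24-month classification, by month 36, but recruits exactly 70 and counts on children who enter too late

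*Protocol article*

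**What the plan says.** All references are to the protocol article.

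- **Two-group size (Sample size calculation, part A).** The inputs are "Assuming a conservative estimate of minimum difference of FMD of 3% between normal and nephrotic syndrome", "with a standard deviation (SD) of 5"%, and "a study with power of 80% at a two-sided 0.05 significance level". They give 46 per group. The section continues "With a 5% attrition rate due to mortality or loss to follow up for the entire study" and raises the figure to a minimum of 50 children with NS and 50 controls for phase I.
- **Late entrants (same section).** NS cases "presenting to the OPD after the 12 months recruitment phase gets over will also be added" to the repository.
- **Three-group size (same section).** The next sentence concludes that, at the end of 36 months, "a minimum of 70 cases each of SSNS, SRNS and healthy controls will be required after final classification of phenotype of NS". The stated purpose is a Bonferroni-adjusted comparison of three means, for both FMD and cIMT. The two institutions are expected to supply this number by month 36.
- **Recruitment (Abstract, Methods).** "70 Steroid Resistant NS (SRNS), 70 Steroid Sensitive (SSNS) patients along with 70 Healthy Controls are being recruited".
- **Timing of classification (Phase ii).** "At the end of 24 months from recruitment for a given case, final reclassification of disease phenotype" is carried out.

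**The concern.** The 70 per group is set as a minimum that must exist after classification, which means after 24 months of follow-up and the losses that come with it. The same 70 appears in the Abstract as the number recruited. The section allows for attrition in the two-group size and shows no such allowance for the three-group size. It also reaches 70 by way of cases added after the recruitment phase, and under the Phase ii rule those children are still unclassified at month 36.

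The comparison of SSNS and SRNS with controls rests on this figure. A reader cannot tell how many classified children that comparison will have at month 36, or what power it has, because neither the number of adjusted tests nor the power behind 70 is stated.

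**Working it through.** **Inputs.** FMD difference 3 and SD 5, so d = 3/5 = 0.6. Power 80%, two-sided 0.05, attrition 5%. For cIMT, the stated difference is 0.03 mm. Taking the SD of 0.05 mm that the section reports for normal children gives d = 0.03/0.05 = 0.6 again, so the sizes below apply to both endpoints.

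**Step 1: the plan's two-group size.** The normal approximation is n = 2(z₁₋α/₂ + z_power)²/d².

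- n = 2(1.960 + 0.842)²/0.36 = 43.6, so 44. The two-sample t-test gives 44.6, so 45. The plan's 46 is within 2 of both.
- 46/0.95 = 48.4, so 49, against the plan's 50.

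The plan's method is therefore clear, and it includes an allowance for loss.

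**Step 2: what could lie behind 70.** Two-sample t-test, α = 0.05/m for m Bonferroni tests, 80% power:

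| m | Reading | α | n per group |
|---|---|---|---|
| 2 | SSNS and SRNS each v control, one endpoint | 0.025 | 54.1 → 55 |
| 3 | three pairwise contrasts, one endpoint | 0.0167 | 59.6 → 60 |
| 4 | two contrasts v control, FMD and cIMT | 0.0125 | 63.5 → 64 |
| 6 | three pairwise contrasts, FMD and cIMT | 0.0083 | 69.0 → 70 |

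Six tests at 80% power give exactly 70. Two tests at 90% power give 70.2, also close to 70. Four tests with 5% loss give 64/0.95 = 67.4, so 68. So 70 can be reached from the plan's inputs in more than one way, and the text does not say which was used.

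**Step 3: attrition.** 70 × 0.95 = 66.5, so about 66 remain. To keep 70 would take 70/0.95 = 73.7, so 74 recruited. Power by t-test, d = 0.6:

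| m | 70 per group | 66 per group | Loss (points) |
|---|---|---|---|
| 2 | 89.9% | 87.9% | 2.0 |
| 3 | 86.8% | 84.5% | 2.3 |
| 4 | 84.4% | 81.8% | 2.6 |
| 6 | 80.7% | 77.7% | 3.0 |

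**Step 4: timing.** A child who enters in study month t is classified in month t + 24. Classification by month 36 requires t ≤ 36 − 24 = 12. All 70 + 70 = 140 classified NS children would therefore have to enter within the 12-month recruitment phase, for which the plan proposes a minimum of 50. Cases added later cannot count by month 36. The document gives neither an accrual rate nor the expected split between SSNS and SRNS, so the size of the shortfall cannot be calculated.

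**The case against.** The strongest reply is that 70 is sound. The sentence names both FMD and cIMT, and Bonferroni over three pairwise contrasts on two endpoints gives exactly 70 at 80% power. This stands. A reader might infer that 70 is an arithmetic error and that 55 or 60 is the true requirement. The document does not support that: those sizes adjust for one endpoint only, and putting 55 in place of 70 would drop cIMT from the adjustment the plan describes. In the other direction, six tests is not the only reading, because the parenthesis in that sentence describes two groups each compared with control. Over two endpoints that makes four tests and 64 per group.

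A second reply is that the loss hardly matters, since 66 keeps power above 80% for two, three or four tests. This also stands. Only with six tests does power fall below 80%, to 77.7%. That is, however, the reading which makes 70 the exact minimum at 80% power.

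A third reply is that 50 is only a minimum for phase I and the Abstract has 140 NS children being recruited, so all of them might enter within 12 months. That is possible, but the text does not say so, and it introduces the month-36 figure as a consequence of adding later cases. A reader might also infer that the phenotype comparisons are severely underpowered at month 36. That would need an assumed intake and phenotype split that the document does not fix.

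Finally, a condensed article may leave the number of tests to a fuller document. For that reason its absence alone is not the point. The conflict between the recruited number, the required number and the date lies within the article.

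**Conclusion.** The point holds as a conflict between the size the plan says it requires and what its design delivers. Recruiting 70 per group with 5% loss leaves about 66, not 70, and children who enter after month 12 cannot be among those classified by month 36.

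The attrition effect is modest: 2 to 3 points of power, leaving about 88% for two tests, 82% for four and 78% for six. These figures rest on the plan's 3% difference, SD of 5% and 5% attrition, with loss spread evenly over the groups and no net movement between phenotypes at reclassification. The timing effect could be larger, but the document does not allow it to be quantified. The 70 itself is not shown to be wrong. Its basis is unstated, and 80% power is compatible with any requirement from 55 to 70 depending on the number of tests.

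**What to change.** No extra enrolment is needed. Three changes to the wording:

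1. State that 70 per group are recruited and about 66 per group are expected after 5% attrition, in place of a minimum of 70 after classification.
2. Name the number of Bonferroni tests and give the matching power for a 3% FMD difference (SD 5%) with 66 per group: about 88% for two tests, 82% for four (two contrasts with control, on FMD and cIMT) or 78% for six.
3. Reconcile the dates. Either make the final-phenotype comparisons when the last included child reaches 24 months, or limit the month-36 comparison to children enrolled in the first 12 months and restate its size and power.

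The cost is a revised sample size paragraph and a slightly less favourable stated number. The first option under item 3 may also move the final-phenotype report beyond month 36.

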### Statistical analysis

Descriptive statistics will be used to characterize the entire population and subgroups of interest at baseline and follow-up. Summary statistics such as means, medians, standard deviations and ranges will be used to describe continuous variables, and frequencies will be tabulated for categorical variables. For outcomes collected longitudinally, Kaplan Meier survival curves, scatter plots and grouped box plots will be used to examine assumptions of survival free of adverse outcome or relapses, and linearity and symmetry of data. Repeated measures analysis will be applied for data derived at multiple time points for same child to study correlation with extent and duration of proteinuria. Cox regression analysis will be applied to analyze the time to event data of the primary or secondary endpoints collected in both cohorts of NS and healthy children and assess association of the outcome hazard with clinical covariates of interest. Correlation of markers of endothelial dysfunction and cIMT will be done with extent and duration of proteinuria as defined by the status of remission and number of relapses per year. cIMT will be used as the gold standard for subclinical vasculopathy for evaluation of association with progression of endothelial function. IMT is chosen for diagnostic evaluation study for other biomarkers of cardiovasculopathy since it is the most well characterized surrogate marker of subclinical atherosclerosis. *P*-value < 0.05 will be considered as significant. Statistical analysis will be performed using SPSS Version 17.0.

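### Plain Bonferroni for SSNS and SRNS versus controls is valid, but a Holm step-down gives more power at the same family-wise error rate and the same sample size

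*Protocol article*

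**What the plan says.** All of this is in the protocol article.

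- **Sample size calculation, part A, two-group comparison.** The inputs are "Assuming a conservative estimate of minimum difference of FMD of 3% between normal and nephrotic syndrome" "with a standard deviation (SD) of 5"%, for a "study with power of 80% at a two-sided 0.05 significance level". The stated result is "a minimum of 46 cases each of NS and healthy controls will be required". The same number is said to suffice for 0.03 mm of cIMT, and 5% attrition brings it to 50 per group.
- **Same part, three-group comparison.** After final phenotype classification, 70 children are needed in each of SSNS, SRNS and controls "for a post-hoc Bonferroni adjustment for comparison of 3 means (2 groups of SSNS and SRNS compared to a control healthy group"), for FMD and cIMT. No power or per-test significance level is given. The text does not say whether FMD and cIMT share one family.
- **Statistical analysis.** The only threshold is that a P-"value < 0.05 will be considered as significant". No multiplicity method is mentioned there.

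**The concern.** With two comparisons under plain Bonferroni, each is judged at 0.025 whatever the other shows. Once one null hypothesis has been rejected at 0.025, only one remains, and it can be tested at the full 0.05 without raising the family-wise error rate. Holm's procedure uses this, and Bonferroni leaves it unused.

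What is at stake is power for the weaker of the two contrasts. The Background section describes lipid disturbance in SSNS as usually transient, and as possibly persistent in frequently relapsing or resistant disease. A smaller SSNS deficit is therefore plausible, though the article gives no figure for it. A fixed 0.025 hurdle costs most when one group is clearly impaired and the other only moderately so.

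The protocol names the method and ties the 70 per group to it, so this is a comment on a stated choice and not on a detail left to another document.

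**Working it through.** **1. The plan's own figure.** For two means, n per group = 2·SD²·(z₁₋α/₂ + z₁₋β)²/δ².
- δ = 3, SD = 5, two-sided α = 0.05, power 80%: 2·25·(1.960 + 0.842)²/9 = 43.6, so 44. A t-test needs 45. The stated 46 is within 2 of both.
- 46/0.95 = 48.4, so 49, against the stated 50.
- The 70 per group has no stated power. With α = 0.05/2 the formula gives 53 at 80% power and 69 at 90%. With α = 0.05/4 it gives 70 at 85%. So 70 is consistent with a Bonferroni design, but the text does not show which one.

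**2. Model for the comparison of methods.** Assumption: two tests, SSNS versus control and SRNS versus control, at 0.05/2 = 0.025 each, for one endpoint.
- Standard error of a difference: 5·√(2/70) = 0.845.
- Expected test statistic: 3/0.845 = 3.55 for each contrast.
- The contrasts share the control group, so their statistics correlate at 0.5 with equal group sizes.
- Critical values: 2.241 for p ≤ 0.025 and 1.960 for p ≤ 0.05.
- Bonferroni, both: P(Z₁ > 2.241 and Z₂ > 2.241).
- Holm, both: P(Z₁ > 2.241 and Z₂ > 1.960) + P(Z₁ > 1.960 and Z₂ > 2.241) − P(Z₁ > 2.241 and Z₂ > 2.241).

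**3. Results at the plan's inputs.**
- Each comparison, Bonferroni: Φ(3.55 − 2.241) = 90.5%.
- Each comparison, Holm: 90.5% + (86.9% − 84.0%) = 93.4%. Here 86.9% is the chance that one contrast passes 2.241 and the other passes 1.960.
- Both, Bonferroni: 84.0%.
- Both, Holm: 2 × 86.9% − 84.0% = 89.9% before rounding of the terms, a gain of 5.9 points.

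**4. Sensitivity of power to show both.**

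| Setting | Bonferroni | Holm | Gain (points) |
|---|---|---|---|
| Plan: 3% in both, SD 5%, n = 70 | 84.0% | 89.9% | 5.9 |
| 67 per group (70 less 5%) | 81.9% | 88.3% | 6.5 |
| SD 4.38% (a value the article reports) | 93.7% | 96.5% | 2.8 |
| Differences 3% and 5% | 90.5% | 94.4% | 3.9 |
| SSNS versus SRNS added as a third test | 79.7% | 84.2% | 4.5 |
| 2.5% in both | 63.8% | 73.6% | 9.8 |
| 2% in both | 38.5% | 49.2% | 10.7 |

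If SSNS differs by 2% and SRNS by 3%, power for SSNS alone goes from 55.0% to 64.8%. That split is an assumption; the article does not give it.

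**5. If FMD and cIMT form one family of four.** The cIMT effect of 0.03 mm with the reported SD of 0.05 mm gives 0.6 SD, the same as 3/5 for FMD. By simulation, with an assumed FMD–cIMT correlation between 0 and 0.8, power to show both FMD contrasts is about 76% with Bonferroni and 87 to 89% with Holm.

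**6. Family-wise error.** In 2,000,000 simulated trials with two comparisons:
- both nulls true: 0.046 for both methods;
- one null true, the other difference 5%: 0.025 for Bonferroni and 0.0498 for Holm.

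Holm stays within 0.05.

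**The case against.** The strongest reply is that nothing here is wrong. Bonferroni is valid, standard and stated. At the plan's inputs it gives about 90% power for each comparison and 84% for both, and still about 82% for both after 5% attrition, which meets the 80% used elsewhere in the section. All of that stands.

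Four further points also stand in part.

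- **Success criterion.** No passage makes impairment in both phenotypes a condition of success, and the primary objective compares NS as a whole with controls. Per comparison the gain is about 3 points.
- **Larger gains.** A reader might infer that the plan gives up as much as 11 points of power. The documents do not support that. The high end needs true differences below the 3% that the plan calls a conservative minimum, a larger SD, or a four-test family.
- **Family of tests.** The 0.025 per test is an assumption. If Bonferroni was meant to cover four tests, running a two-step Holm separately for FMD and cIMT would let the overall error reach about 1 − (1 − 0.046)² = 9% if the endpoints were independent. The change must keep the same family.
- **Intervals and precision.** Bonferroni gives simple matching simultaneous intervals, which suits an objective about the extent of dysfunction. A Holm rejection can sit beside a Bonferroni interval that includes zero. Controls are siblings of cases, so power figures that assume independent groups are approximate.

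None of this changes the direction: over the same family of tests, Holm never rejects less than Bonferroni.

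**Conclusion.** The point holds as an efficiency improvement, not as an error. For the same children and the same family-wise error rate, Holm raises power at the plan's inputs from about 90% to 93% for each comparison and from about 84% to 90% for both. This rests on a 3% difference in both phenotypes, SD 5%, 70 per group, independent groups and two tests per family. The gain for both is about 3 points at SD 4.38% and about 10 points at true differences of 2 to 2.5%.

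A reader might go further and conclude that the three-group comparison is underpowered, or that SSNS would be reported as unaffected because of Bonferroni. The first is not supported at the stated effect. The second depends on an SSNS effect that the article does not quantify.

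**What to change.** - **Sample size calculation, part A.** Replace the post-hoc Bonferroni wording with a pre-planned Holm step-down for SSNS versus control and SRNS versus control, over the same family that the Bonferroni adjustment was meant to cover, and state that family.
  - If control is per endpoint: test the smaller p-value against 0.025 and, if it is significant, the other against 0.05. Step-down Dunnett within an endpoint is an equally good choice, since it uses the shared control group.
  - If FMD and cIMT form one family of four: order the p-values and use 0.05/4, 0.05/3, 0.05/2 and 0.05, stopping at the first that fails.
- **Statistical analysis.** State that this rule overrides the general 0.05 threshold for these comparisons, and say which confidence intervals will be reported, because Bonferroni intervals may not agree with every Holm rejection.

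The cost is a few sentences. Sample size, visits and data collection do not change.
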